**2.2. Method of Assignment to Treatment**

Subjects who meet all criteria for enrollment will be randomized to double-blind treatment. Randomization will be performed and assigned independently by a statistician working in an independent institution, held centrally, and not divulged to any other person involved in the trial until after database lock. We will adopt a simple randomization procedure scheme.

**2.3 Statistical and Analytical Plans**

**2.3.1. General Considerations**

Unless otherwise noted, all tests of treatment effects will be conducted at a 2-sided alpha level of 0.05; 2-sided confidence intervals will be displayed with a 95% confidence level. All tests of interactions between treatment and other factors will be conducted at an alpha level of 0.05. All analyses will follow the intent-to-treat (ITT) principle unless otherwise specified. An ITT analysis is an analysis of data by the groups to which subjects are assigned by random allocation, even if the subject does not take the assigned treatment, does not receive the correct treatment, or otherwise does not follow the protocol.

**2.3.2. Analysis Populations**

Baseline characteristics as well as the co-primary and secondary efficacy measures will be summarized for the ITT and per-protocol populations by treatment group and overall. Tabulations of the number and percentage of subjects included in each analysis set, by treatment group and overall, will be provided. Reasons for exclusion from analysis datasets will also be provided.

**2.3.3. Patient Characteristics**

The patient’s age, gender, height, body weight, tobacco use, alcohol use, caffeine use, years of education, work status, time since onset of first FTD symptoms, time since diagnosis, MMSE and CDR at Visit 1, and concomitant drug use at baseline will be recorded. Baseline characteristics will be summarized for the ITT and per-protocol populations by treatment group and overall. Summaries will include descriptive statistics for continuous and categorical measures. Pearson’s chi-square test will be used for treatment group comparisons of categorical data. For continuous data, t-test or corresponding non-parametric test (Mann-Whitney) will be used for the group comparing.

**2.3.4. Analysis of Efficacy Outcomes**

Normality assumption of end-points variables will be assessed by inspection of the distribution plots and by Kolmogorov-Smirnov and Shapiro-Wilk tests. Preliminary descriptive analyses will be performed by means, frequencies, standard deviations (SD) and percentages. Comparison of socio-demographic and clinical features between the study groups at baseline will be performed through t-test or Mann-Whitney tests. The longitudinal assessment of the end-points across groups will be performed through Generalized Linear Mixed Model (GLMM) for repeated measures with random intercept and random slope to account for individual differences at baseline as well as for individual change after the treatment. GLMMs will be applied to FTLD-CDR SoB and the other efficacy outcome measures, MMSE, ACE-R, FBI, SAND, ADCS-ADL, FAB and NPI, as dependent variables (one model for each outcome measure), and group, time and group x time interaction as independent factors. In detail, analysis of residuals (after adjustment for variables that mainly affect the outcomes: age and education) led us to adopt GLMMs for Gaussian data with identity link function for FTLD-CDR SoB, SAND, FBI, ACE-R, MMSE, ADCS-ADL and FAB; whereas GLMM for Negative binomial data, with log-link function, will be used for NPI. The GLMMs on MMSE and FAB will be adjusted for age and education.

TEPs analysis will be conducted in two steps. First, to identify the exact the TEP time windows at which there will be a significant difference, we will perform multiple t-tests (corrected with false discovery rate method) at each time point of the TEP waveform from -100 to 300 ms after TMS. This analysis will be conducted for each group (PEA-LUT group vs placebo) and for each evaluation (baseline W0 vs W24). Once detected the significant time windows, we will compare the mean TMS-evoked activity (dependent variable) within these intervals with a generalized linear mixed model (GLMM -for Gaussian data-) for repeated measures with group (real vs. sham), time (W0 vs. W24) and “window” as independent factors. TRSP analysis will be conducted with dependent t-tests comparing the different frequency bands (alpha, beta, gamma, theta) in the two time points of evaluation (W0 and W24). Safety analyses for the treatment period will include comparisons between PEA-LUT group and placebo groups by 2-sided 0.05 significance level Chi-square tests. Statistical analyses will be performed with IBM SPSS statistics, version 24.0 and R software; significance alpha level test is set up at 0.05.

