To evaluate cortical activity, in terms of TMS-evoked potentials (TEPs) and oscillations in the left and right dorsolateral prefrontal cortex (DLPFC) we used TMS-EEG. Indeed, it has been suggested that early TEPs originate from GABA(A)-mediated and GABA(B)-mediated inhibitory post synaptic potentials (IPSPs) (*Rogasch et al., 2013*). On the other hand, TMS-evoked oscillations allow to investigate the natural frequency of a target area and to assess the thalamo-cortical circuits. After one month of PEA-LUT treatment, we observed a significant amelioration in the behavioural symptoms and in frontal executive functions. Neurophysiological results showed a remarkable improvement of GABA(B) activity as revealed by a restoration of decreased LICI. We also observed an increase of LTP- like cortical plasticity after PEA-LUT treatment. These results were quite specific since we did not find any change in the other protocols assessing GABA(A)-ergic activity (SICI) nor cholinergic activity (SAI). We also found a significant increase in TMS-evoked oscillations in both left and right DLPFC. In particular, such increase was prominent for high-frequency oscillations, such as beta (14-30 Hz) and gamma power (30-45 Hz). TEPs evaluation revealed a significant increase of cortical excitability both in left and right DLPFC, in particular in GABA(B)-mediated TEPs, between 60 and 100 ms after TMS. Taken together, these preliminary results seems to suggest that PEA-LUT could be able to reduce behavioural disturbances and improve executive functions; moreover these results show that one month of PEA-LUT can restore cortical plasticity and GABA(B) activity, which seem to be compromised in FTD patients (*Murley et al., 2018*). Finally PEA-LUT is able to restore high-frequency oscillations that are reduced between the frontal lobes of FTD patients.

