**6)** Global Cognition [Time Frame: change from baseline to week 24]: Addenbrooke's Cognitive Examination Revised (ACE-R)The scores range from 0-100 with a higher score meaning less cognitive impairment.

**7)** Global Cognition [Time Frame: change from baseline to week 24]: Mini Mental State Examination (MMSE). The scores range from 0-30 with a higher score meaning less cognitive impairment.

**8)** TMS-evoked EEG responses, in terms of potentials (i.e., TEPs) and oscillations (i.e., TRSP) as a novel probe of cortical excitability changes induced by PEA-LUT. TEPs and TRSP will be computed by stimulating the left and right DLPFC and simultaneous electroencephalography recordings over all the scalp.

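### The TEP window search starts 100 ms before the TMS pulse, so pre-pulse EEG can be scored as evoked activity, and a quarter of the FDR family lies where no evoked response can exist

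*Combined protocol and SAP*

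**What the plan says.** The protocol's list of secondary efficacy measures (section 1.9, item 8) names "TMS-evoked EEG responses, in terms of potentials (i.e., TEPs) and oscillations (i.e., TRSP) as a novel probe of cortical excitability changes" as the neurophysiological outcome, with stimulation of the left and right DLPFC.

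SAP section 2.3.4 derives the TEP part in two steps.

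- **Step 1, finding windows.** The method is given as "we will perform multiple t-tests (corrected with false discovery rate method", and the range searched is set as "at each time point of the TEP waveform from -100 to 300 ms after TMS". The comparisons are described thus: "This analysis will be conducted for each group (PEA-LUT group vs placebo) and for each evaluation (baseline W0 vs W24".
- **Step 2, testing them.** "Once detected the significant time windows, we will compare the mean TMS-evoked activity (dependent variable) within these intervals", using a Gaussian mixed model with group, time and window as factors.

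The only significance level given is general: "significance alpha level test is set up at 0.05". The FDR procedure and its level are not named. No section restricts windows to times after the pulse, calls -100 to 0 ms a baseline or control interval, or describes baseline correction. The pilot TEP finding reported in section 1.4 lay after the pulse: "in particular in GABA(B)-mediated TEPs, between 60 and 100 ms after TMS".

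**The concern.** The outcome is a response to the pulse, but the rule that produces it also searches 100 ms in which no pulse has been given. The wording is at odds with itself, since -100 ms is not after TMS. Two things follow.

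1. A significant pre-pulse stretch becomes a level of the window factor and is analysed as evoked activity, which the definition in section 1.9 rules out.
2. The pre-pulse points count in the FDR family and tighten the threshold for the points where a TEP can lie.

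The first risk grows when the treatment works. Each true discovery after the pulse relaxes the step-up threshold for the whole family, including the pre-pulse points. At stake is the meaning of the TEP measure, through which the trial hopes to show a change in cortical excitability, and a little of the power to detect that change.

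This differs from the problem of choosing and testing windows on the same recordings. Separate selection data would not prevent a pre-pulse window from being chosen.

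**Working it through.** The plan gives no family size or error rate for this search, so there is no stated figure to reproduce.

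**Inputs from the documents.** Search interval -100 to 300 ms and alpha 0.05 (SAP 2.3.4); pilot latency 60-100 ms (protocol 1.4); 25 and 23 patients (SAP 2.1).

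**Assumptions.** Benjamini-Hochberg at q = 0.05; a 1 ms grid; one averaged channel; Gaussian noise with correlation scale 5, 10 or 20 ms; a standardised effect of 0.93. The 0.93 is borrowed from SAP 2.1, where it is a pre-post effect on cognitive and behavioural scores, not an EEG effect. The documents give no sampling rate or EEG variance.

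**Pre-pulse share.** 100 / 400 ms = 25%. Counting grid points: 25/101 = 24.8% at 250 Hz, 50/201 = 24.9% at 500 Hz, 100/401 = 24.9% at 1 kHz, 500/2001 = 25.0% at 5 kHz. The share hardly depends on the sampling rate.

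**Cut-off.** Benjamini-Hochberg compares the k-th smallest p-value with qk/m. Over the full interval this is 0.05k/400; over post-pulse points only it is 0.05k/300. The ratio is 300/400 = 0.75, so the full-interval cut-off is 25% stricter at every rank. On the exact 1 kHz grid (401 against 300 points) the post-pulse cut-off is 401/300 = 1.34 times as large.

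**Why a real effect raises pre-pulse flags.** With no other rejections, a single point must reach 0.05 × 1/401 = 0.000125. If all 41 points from 60 to 100 ms are rejected, the cut-off at that rank is 0.05 × 41/401 = 0.0051, and null pre-pulse points are judged against roughly that value.

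**Simulation, between-group comparison.** 25 against 23 patients, pointwise t-tests, 0.93 SD effect at 60-100 ms only, no baseline correction. Ranges in the second column are over repeated runs.

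| Noise scale | Any pre-pulse point flagged | At least 10 consecutive pre-pulse points | Post-pulse detection: full family → post-pulse only |
|---|---|---|---|
| 5 ms | about 7-9% | 0.3% | 91.0% → 92.6% |
| 10 ms | about 4-5% | 2.1% | 76.5% → 80.3% |
| 20 ms | about 2-3% | 1.6% | 63.2% → 66.9% |

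With no effect anywhere, a pre-pulse point is flagged in about 1% of comparisons or fewer.

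**Simulation, paired comparison.** With paired tests (n = 24), effects of 0.6 to 0.93 SD and scales 5 and 10 ms, a pre-pulse point was flagged in about 3-11% of comparisons. Subtracting each patient's pre-pulse mean did not remove the risk: at 0.93 SD, 10.7% became 8.4% at scale 5 ms, and 5.2% became 5.0% at scale 10 ms. Average pointwise power within 60-100 ms rose by about 2 to 5 points under post-pulse-only testing, for example from 0.32 to 0.37 at 0.6 SD and from 0.73 to 0.77 at 0.8 SD.

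**Cost of the looser cut-off.** At scale 10 ms, the chance of flagging at least one null post-pulse point (outside 60-100 ms) rose from 10.5% to 13.7%. In another set of runs it rose from 18.3% to 23.5%, 11.7% to 14.6% and 6.3% to 8.2% at scales 5, 10 and 20 ms. The nominal FDR level is unchanged.

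**The case against.** The strongest defence is that the plan's own vocabulary settles the matter. Step 1 looks for TEP windows, step 2 averages TMS-evoked activity, and a pre-pulse stretch is neither. On this view -100 to 0 ms was a baseline or display interval, and any competent analyst would discard a window found there. That may well be the intention, but the text names -100 to 300 ms as the range tested and contains no such exclusion. Discarding a window once its significance is known would be an unwritten, post hoc decision.

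Other parts of the defence stand.

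- Most flagged pre-pulse stretches are very short, and their latency gives them away.
- Limiting the family admits somewhat more null post-pulse points, which look more plausible as TEPs.
- For a chance pre-pulse window to be reported as a treatment effect depends mostly on testing it in the recordings that selected it. In independent data it would be null apart from ordinary 5% error.

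A reader might also infer more than the documents support.

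- **Compounding over comparisons.** The text can be read as four comparisons at each of two sites, which invites raising the per-comparison rate to eight. The count is not stated. Half of those comparisons should carry no drug effect (the arms at baseline, and placebo over time). Comparisons that share recordings are not independent.
- **A broad effect.** An effect spread over most of the post-pulse interval would flag pre-pulse points much more often, but the pilot singles out 60-100 ms and nothing in the documents supports the broader pattern.
- **Distortion of the estimated effect.** Window is a factor in the model, so a pre-pulse level may simply receive its own estimate. No mixed model was simulated, and distortion has not been shown.

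**Conclusion.** The point holds as a defect in a stated rule. Section 2.3.4 can admit EEG that the outcome's definition excludes, and it spends a quarter of its FDR family before the pulse. The 25% share and the 25% stricter cut-off follow directly from the stated interval; the cut-off also assumes Benjamini-Hochberg.

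The practical size is modest. In the between-group simulation about 2-9% of comparisons flag at least one pre-pulse point when there is a 60-100 ms effect, about 1% or less flag one when there is none, and runs of 10 ms or more occur in about 0-2%. Detection improves by about 2-5 points when only post-pulse samples are tested. These rates rest on the assumed effect, grid, noise smoothness and single channel.

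Only a secondary neurophysiological measure is affected. The documents give no reason to extend the point to the FTLD-CDR SoB analysis or the other clinical scales. The change is still worth making because it costs almost nothing.

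**What to change.** In the TEP paragraph of SAP section 2.3.4:

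1. Replace the search range with one running from the first artefact-free sample after the pulse to 300 ms. Fix that first latency as a number before unblinding.
2. State that the FDR family consists of those samples only, and that no pre-pulse window may enter the mixed model.
3. State that -100 to 0 ms serves only for baseline correction, or as a separate descriptive check that arms and visits do not differ before the pulse.

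The cost is a sentence or two in the SAP and a changed index range in the EEG analysis code. It needs no new data and changes nothing for patients. The trade is a small gain in detection against a slightly higher chance of flagging a null post-pulse point (for example about 10.5% to 13.7% at noise scale 10 ms), at the same nominal FDR level.

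### Step 2 of the TEP analysis tests windows that were chosen for significance in the same recordings, so its p-values and effect sizes are not valid once a window has been selected

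*Combined protocol and SAP*

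**What the plan says.** SAP section 2.3.4 analyses TEPs in two steps.

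- **Step 1** is run "to identify the exact the TEP time windows at which there will be a significant difference". The method is: "we will perform multiple t-tests (corrected with false discovery rate method) at each time point of the TEP waveform from -100 to 300 ms". On the contrasts it says: "This analysis will be conducted for each group (PEA-LUT group vs placebo) and for each evaluation (baseline W0 vs W24". This can be read as visit comparisons within each arm, arm comparisons at each visit, or both. The FDR level is not given.
- **Step 2** takes the windows found: "Once detected the significant time windows, we will compare the mean TMS-evoked activity (dependent variable) within these intervals with a generalized linear mixed model". The model is a Gaussian GLMM "for repeated measures with group (real vs. sham), time (W0 vs. W24", and window as a third factor. The decisive term is not named.

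Protocol section 1.6 (Evaluation Phase) places neurophysiology at baseline and week 24 only, so no separate trial recordings exist from which to choose windows. Section 1.9 lists TEPs within secondary efficacy measure 8. The SAP gives no fixed window, no selection contrast independent of treatment and no error control spanning both steps, and does not call step 2 descriptive. The pilot results in section 1.4 do point to an interval ("in particular in GABA(B)-mediated TEPs, between 60 and 100 ms after TMS"), but the SAP does not use it.

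**The concern.** A window enters step 2 because the arms, or the visits, already differ there. Step 2 then asks about group and time in that window with the same patients and recordings. Part of what it finds is the chance deviation that caused the selection, so a nominal 5% test no longer has a 5% error rate given selection, and the estimate is too large on average.

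The FDR correction limits false discoveries among time points in step 1. It does not adjust the step-2 p-value or estimate for selection, and these are the figures likely to be reported as the effect on cortical activity. The search interval also includes 100 ms before the pulse, where no evoked response can exist.

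**Working it through.** The plan states no power, effect size or error rate for TEPs, so there is no figure of its own to reproduce.

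**Inputs from the documents.** 25 and 23 patients (SAP 2.1); two recordings per patient (section 1.6); search from -100 to 300 ms with FDR (SAP 2.3.4); two-sided alpha 0.05 (SAP 2.3.1).

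**Assumptions.** FDR by Benjamini-Hochberg at 0.05; 1 ms sampling; one averaged waveform per patient and site; Gaussian smoothing SD 5 to 10 ms; retest correlation r of 0.5 to 0.7; noise SD 1.

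**1. Is selection independent of group x time?** Let D be the arm difference in change from W0 to W24. With equal variances at both visits, the correlation of each selecting contrast with D is:

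- change within PEA-LUT: sqrt(23/48) = 0.69; change within placebo: sqrt(25/48) = 0.72;
- arm difference at one visit: sqrt((1 - r)/2) in absolute value = 0.50 at r = 0.5 and 0.39 at r = 0.7;
- grand average over both arms and both visits: 0, because the sum of the two visits is uncorrelated with their difference.

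Neither reading of step 1 gives independence; the grand average does.

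**2. Rough size by hand.** If a selected window has z in the selecting contrast (z of 3 to 4 assumed) and c is the correlation above, the z for D is about normal with mean c x z and SD sqrt(1 - c^2). For PEA-LUT at z = 3.5: mean 0.692 x 3.5 = 2.42, SD 0.72, so P(z > 1.96) is about 74% (56% at z = 3, 87% at z = 4). For an arm difference with r = 0.5: mean 1.75, SD 0.87, about 40% (30% to 52%).

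**3. Simulation with no effect and no change.** 1,500 trials per setting. Group x time is a two-sample t-test on change in the window mean, equivalent to the Gaussian mixed-model interaction for two complete visits. A trial counts as a rejection if any selected window rejects.

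| Selection | Window found | Group x time rejects, given a window | Unconditional |
|---|---|---|---|
| Within arm (4 settings) | 5.7-6.1% | 71-86% | 4.2-5.3% |
| Between arms (4 settings) | 5.2-5.9% | 30-50% | 1.6-2.6% |
| Both (smoothing 5 ms, r = 0.5) | 11.1% | 65% | 7.2% |
| Fixed 60-100 ms | n/a | n/a | 4.2-5.7% |

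The last column is the product of the other two, e.g. 0.111 x 0.651 = 0.072. Repeated runs at smoothing 8 ms and r = 0.6 gave 68-85% (within arm) and 31-43% (between arms) given a window, and about 6% unconditionally per site.

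The pre-pulse part is 100 of 400 ms, or 25% of the search. Accordingly, 20-31% of null windows lay wholly before the pulse.

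**4. Both arms change equally, no treatment effect.** With a shared peak change of 0.5 SD (smoothing 5 ms, r = 0.5) and within-arm selection, a window is found in 64.7% of trials and group x time rejects in 45.8% of those: 0.647 x 0.458 = 30% unconditionally. Using only windows from PEA-LUT: 0.427 x 0.367 = 16%. At smoothing 8 ms and r = 0.6, shared changes of 0.3 to 0.5 SD gave about 10-15%. A fixed window stayed at 4-5%.

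**5. Size of a true effect.** With a peak effect of 0.5 SD, the mean absolute estimate in selected windows was 0.707 against a true window mean of 0.311 (ratio 2.3) for within-arm selection, and 0.630 against 0.254 (ratio 2.5) for between-arm selection. With a true effect of 0.30 SD at smoothing 8 ms, windows chosen from the change within PEA-LUT averaged 0.51 (ratio 1.7); another run at that smoothing gave about 1.5. At the 0.5 SD peak, the 60-100 ms window detected the effect in 54-55% of trials, against 10-26% for the two-step plan.

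**The case against.** The best defence is the FDR gate. With no effect and no change over time it usually stops the procedure before step 2, and the unconditional group x time error stays near nominal. At smoothing 8 ms and r = 0.6, over both stimulation sites, the two-step plan gave 11.0% and a fixed window 9.5%, so in that scenario the remedy gains little. This stands. A reader might infer from the conditional rates that most null trials would report a false TEP effect, or that FDR gives no protection; neither follows. The gate fails in two narrower respects: it leaves the reported p-value and estimate biased once a window is found, and it opens readily when both arms change together, which is plausible over 24 weeks of a progressive disease.

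Other stronger readings also go too far:

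- *That the step-1 contrasts are exactly those tested in step 2.* Step 1 tests simple effects. They overlap with group x time but are not the same contrast.
- *That chance arm differences at baseline must regress into a false interaction.* This route exists only under the between-arm reading, and even then it does not always produce a rejection.
- *That no TEP result could be read as a treatment effect.* Under the between-arm reading, the FDR-corrected week-24 comparison in step 1 is itself a randomised comparison. Only step 2 is circular.
- *That the 61 recording sites make matters worse.* The SAP does not say how channels are combined or whether FDR spans them, so this cannot be quantified.

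Finally, TEPs are one part of a secondary measure in a phase IIa study, which limits the consequence.

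**Conclusion.** The point holds for step 2 of the TEP measure and should be fixed; it does not bear on the primary FTLD-CDR SoB analysis or the clinical secondary scales. Under either reading of step 1, selection is correlated with group x time. Given a selected window and no true effect, a 5% test rejects in about 68-86% of cases (within-arm selection) or 30-50% (arm-difference selection), and true effects are overstated about 1.5 to 2.5 times. Unconditionally, the error is about 2-7% per site when nothing changes, and about 10-30% when both arms share a change.

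The rates depend on the assumed smoothness, retest correlation, FDR level and shape of the shared change. They also depend on testing each selected window separately, whereas the SAP's model carries window as a factor and does not say which term decides. The direction was the same in every setting tried.

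**What to change.** Amend SAP section 2.3.4 before unblinding, in one of two ways.

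1. **Fix the windows.** Set post-pulse windows independently of group x time, then run the GLMM once with group x time as the stated test. One source is the pilot's 60-100 ms, with the caveat that it comes from 18 patients assessed before and after one month of treatment, with no comparator described. The other is the grand average over both arms and both visits.
2. **Use one test.** Make a single cluster-based permutation test of the arm difference in W24 - W0 change, from 0 ms onward, the only inference, and label any window summaries descriptive.

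Under either option, state which comparisons are made and do not search before the pulse. The cost is SAP wording. The drawback of a fixed window is that it can miss an effect elsewhere in the waveform, which can be reported as exploratory.

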**Secondary Objective:**

The secondary objectives of this study are as follows:

- To test the hypothesis that PEA-LUT will slow the rate of decline associated with FTD in the activities of daily living, as assessed with the Alzheimer's disease Cooperative Study Activities of Daily Living (ADCS-ADL), using a GLMM for repeated measures.
- To assess benefit of treatment with PEA-LUT on frontal cognitive functions, as demonstrated through the Frontal assessment battery (FAB), using a GLMM for repeated measures.
- To evaluate efficacy of treatment with PEA-LUT on behavior, as demonstrated through the Neuropsychiatric Inventory (NPI) and Frontal Behavioral Inventory (FBI), using a GLMM for repeated measures.
- To evaluate efficacy of treatment with PEA-LUT on language function, as demonstrated through the Screening for Aphasia in Neurodegeneration (SAND) using a GLMM for repeated measures.
- To evaluate efficacy of treatment with PEA-LUT on global cognition, as demonstrated through the Addenbrooke's Cognitive Examination Revised (ACE-R) and Mini Mental State Examination (MMSE) using a GLMM for repeated measures.
- To evaluate changes from Baseline to Week 24 in the TMS/EEG protocol, to evaluate effects of PEA-LUT on DLPFC cortical activity, oscillatory activity and connectivity.
- Nature, frequency and severity of adverse events (AEs): to assess the safety and tolerability of PEA-LUT given for up to 24 Weeks.

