**Evaluation Phase**

During the week before starting PEA-LUT administration, and during the week at the end of 4th (W4), 12th week (W12) and 24th week (W24) FTD patients will undergo clinical assessment. Neurophysiological assessment will be performed at baseline and W24 and the evaluation will be done in two different days.

1) Clinical Assessment: before and after the 24 weeks of treatment FTLD-CDR SoB, FAB, MMSE, SAND, ACE-R, FBI, ADCS-ADL, FAB and NPI will be administered.

2) Neurophysiological assessment: for TMS-EEG recordings, a TMS-compatible EEG equipment will be used for recording EEG activity from the scalp (BrainAmp, BrainProducts). The EEG will be continuously acquired from 61 scalp sites positioned according to the 10-20 International System. TMS-EEG recordings will be performed over the right and left DLPFC. To precisely position the coil over the cortical sites across different sessions, a neuronavigation system (Softaxic, E.M.S.) will be used. During the TMS-EEG session, DLPFC will be stimulated with 80 single TMS pulses (Koch et al., 2018).

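### The second-step TEP model names group, time and window but no group-by-time term, so no stated TEP test compares the baseline-to-Week-24 change between PEA-LUT and placebo

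*Combined protocol and SAP*

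**What the plan says.** The TMS-EEG objective in protocol Section 1.5 (Secondary Objective) is "To evaluate changes from Baseline to Week 24 in the TMS/EEG protocol, to evaluate effects of PEA-LUT on DLPFC cortical activity", together with oscillatory activity and connectivity. Section 1.6 (Evaluation Phase) fixes the visits: "Neurophysiological assessment will be performed at baseline and W24".

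SAP 2.3.4 analyses TEPs in two steps. Step one screens the waveform with pointwise t-tests under false-discovery-rate control, by group and by evaluation, to find time windows. Step two compares mean activity in those windows with a Gaussian mixed model "for repeated measures with group (real vs. sham), time (W0 vs. W24) and" window as the independent factors. No interaction is named, and no term is identified as the test of treatment.

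Earlier in the same section, the models for FTLD-CDR SoB, MMSE, ACE-R, FBI, SAND, ADCS-ADL, FAB and NPI are given "and group, time and group x time interaction as independent factors". TEPs are not in that list.

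SAP 2.3.1 adds: "All tests of interactions between treatment and other factors will be conducted at an alpha level of 0.05". It does not say which models contain an interaction.

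**The concern.** With two arms and two visits, an effect of PEA-LUT on change is the group-by-time interaction. A model holding only the three listed factors has no such term. Its group test compares the arms on activity averaged over Week 0 and Week 24, and Week 0 precedes treatment. Its time test asks whether activity changed in both arms taken together.

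The rest of the TEP and oscillation plan does not supply the missing comparison. Step one states no between-arm comparison of change, and the oscillation analysis (TRSP) uses dependent t-tests of Week 0 against Week 24.

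At stake is whether the TEP part of this secondary objective receives the test it needs. A real effect could be missed through a diluted group test, and a reader of the results would not know in advance which term was meant to carry the conclusion. The gap would remain even if the windows were fixed beforehand.

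**Working it through.** **The plan's own figure.** SAP 2.1 gives 18 per group for power 0.95 with a paired Wilcoxon test, effect size 0.93 and two-sided alpha 0.05. Using a paired noncentral-t calculation with n scaled by the Wilcoxon efficiency 3/π, n = 18 gives 0.951 and n = 17 gives 0.9385, so 18 reproduces. It concerns a pre-post comparison and has no bearing on the TEP model, for which the plan gives no sample-size figure.

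**Inputs.** From the documents: 25 and 23 patients (SAP 2.1), two-sided alpha 0.05 (SAP 2.3.1), two visits (Section 1.6), simple randomization (SAP 2.2). Assumed: SD 1 at both visits, within-patient correlation r, and Week 24 effect Δ in SD units. One value per patient per visit is used, so window and side of stimulation are left out.

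**What each term estimates.** Let b be the baseline difference between arms and p the placebo change.

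- Group, main effects only: [b + (b + Δ)]/2 = b + Δ/2.
- Time, main effects only: p + Δ × 25/48, roughly p + Δ/2.
- Group by time: (b + Δ) − b = Δ.

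A mixed-model fit to 2,000 simulated patients with two windows agreed. With b = 0.3, p = −0.4, Δ = 0.8 and equal arms, the main-effects model gave group 0.67 (expected 0.70) and time 0.00 (expected 0). Adding the interaction gave 0.77 (SE 0.03) for the true 0.8.

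**Power.** The variance of a patient's two-visit mean is (1 + r)/2 and that of the change is 2(1 − r). With K = √(25 × 23/48) = 3.461 and 46 degrees of freedom, the noncentralities are

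- group: K × (Δ/2)/√((1 + r)/2)
- group by time: K × Δ/√(2(1 − r))

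and their ratio is √((1 − r)/(1 + r)): 0.73 at r = 0.3, 0.58 at 0.5, 0.42 at 0.7 and 0.33 at 0.8. It is below 1 for every positive r.

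Example, Δ = 0.93 and r = 0.5: group 3.461 × 0.465/0.866 = 1.858, power 44%; group by time 3.461 × 0.93/1 = 3.219, power 88%.

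| Δ (SD) | r | Group | Group by time |
|---|---|---|---|
| 0.93 | 0.3 | 50% | 76% |
| 0.93 | 0.5 | 44% | 88% |
| 0.93 | 0.7 | 40% | 98% |
| 0.93 | 0.8 | 38% | above 99% |
| 0.5 | 0.5 | 16.5% | 40% |
| 0.3 | 0.5 | 9% | 17% |

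At r = 0.5 the loss is about 44, 23 and 8 percentage points at 0.93, 0.5 and 0.3 SD.

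**The case against.** The strongest reply is that listing factors in a repeated-measures design is often shorthand for the factorial model. The TEP paragraph never says main effects only, SAP 2.3.1 anticipates treatment interactions, and the real-versus-sham label in a trial with no sham arm suggests loose drafting rather than a deliberate model. This stands as a caution about intent. It does not close the gap: the same section names the interaction when it wants one, and even a full factorial would leave open which term tests efficacy.

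Two stronger readings are tempting, and the documents support neither.

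- *The group test is invalid.* It is not. Under randomization the expected baseline difference is zero, so the test is a valid between-arm comparison with expectation Δ/2. Chance imbalance adds noise that the standard error already covers. The defect is dilution, and that it is not a test of change.
- *The plan will report a time effect as a drug effect.* No section names the time term as evidence of efficacy. If both arms shifted by an assumed 0.5 SD with no drug effect, the time term would reject in about 92% of trials at r = 0.5 (53% at 0.3 SD, 10% at 0.1 SD). Those are correct rejections of the time null and do not demonstrate a false drug claim.

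It is also fair to object that 0.93 is a pre-post effect from cognitive and behavioural results. It is neither a TEP effect nor a between-arm difference, so the power loss must be read across the range shown.

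**Conclusion.** The point holds as a gap in specification. As written, no stated TEP test compares the Week 0 to Week 24 change between PEA-LUT and placebo. Under the literal model the only between-arm test is the group term, which carries half the effect.

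The cost in power runs from about 8 points (0.3 SD, r = 0.5) to about 61 points (0.93 SD, r = 0.8) over the settings tabulated. It rests on the assumed effect size, correlation and equal visit variances; with unequal variances or a random slope the visit average would be differently weighted.

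The scope is one secondary measure. The primary FTLD-CDR SoB analysis and the clinical secondary analyses already include group by time and are unaffected.

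**What to change.** In the TEP paragraph of SAP 2.3.4:

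1. Specify group, time, window, group by time and group by time by window, with the lower-order window interactions that the three-way term implies and patient as random effect.
2. Name the overall group-by-time contrast, PEA-LUT minus placebo in the Week 24 minus Week 0 change, as the single test of treatment effect.
3. Report per-window contrasts as supportive, with a stated multiplicity adjustment.
4. State that the group and time main effects are not evidence of efficacy.
5. Relabel the group factor as PEA-LUT versus placebo.

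This costs SAP wording and a few extra parameters, and no new data. An overall contrast averages over windows, so opposite effects in different windows would cancel; the supportive contrasts would show that. The nominal 5% error rate of the new test assumes windows not selected from the same data. Step one does select them that way, which is a separate issue that this change does not resolve.
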